### Clinical endpoints

Beyond information on demographics, medical history and genetics (where applicable) in the global DRE population, the registry aims to gather a broad range of clinical outcome measures to assess the purported benefits of VNS. The clinical endpoints of the registry include data collection at baseline as well as 3, 6, 12, 24 and 36 months after implant. Long-term follow-up data may continue annually through 60 months after implant where applicable (table 2).

**Table 2 T2:** Protocol-specified visit schedule and assessments for participants in the CORE-VNS registry. After the first year, patients will return to the clinical site for annual visits, where all endpoint measures will be assessed. At unscheduled visits, only VNS parameter settings, concomitant treatment for epilepsy and safety data will be collected

Target follow-up	Baseline	Implant	Follow-up (post implant)					
	−45 to 5 days before implant	0	Titration visit(s)	3 months (±45 days)	6 months (±45 days)	12/24/36 months (±45 days)	Long-term follow-up *Every 12 months until 60 months or study end (±60 days*)*	Unscheduled visits
Informed consent/assent/data privacy	X							
Inclusion/exclusion criteria	X							
Demographics and medical history	X							
VNS Therapy implant/revision/explant		X	*As needed*	*As needed*	*As needed*	*As needed*	*As needed*	*As needed*
VNS Therapy parameter settings		X	X	X	X	X	X	X
Concomitant treatments for epilepsy†	X			X	X	X	X	
Rescue medication use	X			X	X	X	X	
Seizure frequency	X			X	X	X	X	
Maximum seizure-free period	X			X	X	X	X	
Seizure severity/postictal severity	X			X	X	X	X	
Quality of life	X			X	X	X	X	
Quality of sleep (PSQI or CSHQ)‡	X			X	X	X	X	
Healthcare utilisation	X			X	X	X	X	
VNS Therapy feature use (if applicable)			X	X	X	X	X	X
Deaths and AEs related to VNS (if applicable)§		X	X	X	X	X	X	X
Pregnancy reporting form (if applicable)	*As needed*	*As needed*	*As needed*	*As needed*	*As needed*	*As needed*	*As needed*	*As needed*
Device deficiencies (if applicable)		X	X	X	X	X	X	X
Study completion or withdrawal			*At study exit*	*At study exit*	*At study exit*	*At study exit*	*At study exit*	*At study exit*

*During the long-term follow-up phase, subjects will have yearly follow-up visits until 60 months post implant or until study end (whichever comes first).

†Pharmacological and non-pharmacological.

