### Healthcare resource utilisation

The number of seizure-related emergency department (ED) visits and seizure-related hospitalisations, as well as the duration of those stays, that have occurred since the previous visit are collected at each visit. At the baseline visit, these outcomes are collected through the previous 12 months. Clinical visits related to VNS programming are also collected.

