Principal analysis of the full cohort data will occur at 3 years of follow-up and will be summarised using descriptive statistics for the relevant analysis population (mSAF or FAS). Intermediate analysis will also be conducted for the full cohort at each year after implant, and topics of this analysis are further described in the following section. Continuous variables will be summarised using the number of observations, mean, median, SD, minimum and maximum values. Categorical variables will be summarised using the number of observations and percentages. Absolute scores and changes from baseline with 95% CIs will be reported for each clinical endpoint at each follow-up visit. VNS-related adverse events, including serious adverse events and deaths, will be presented by system organ class and preferred term as total counts and percentages. These adverse events will be further described by their relationship to VNS implant and/or stimulation and the current status (eg, ongoing, resolved, death, chronic or unknown).

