### Healthcare resource utilisation by people receiving VNS

The DRE population uses a disproportionate amount of the healthcare resources accounted for by people with epilepsy, which is characterised in the skewed nature of epilepsy healthcare cost distributions.^32^ Costly ED visits are significant drivers of the healthcare resource utilisation in this population. We will assess, on a regional basis, how VNS impacts ED utilisation and overall healthcare utilisation. We will also assess whether utilisation of scheduled programming can reduce the number of office visits required to titrate patients to dose.

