The design of CORE-VNS allows for a prospective assessment of programmed settings through the titration window. In many people, these settings are collected in electronic records along with other clinical and safety outcomes data. Such records are not collected at titration visits, which do not assess clinical and safety outcomes. To mitigate this, an electronic capture of the programming history from each programming tablet will be used in the registry. These data will be used to develop a clear picture of the titration period from each site and aim to eliminate the risk of missing data fields in titration logs.

Lastly, COVID-19 has impacted this registry both from a recruiting and follow-up perspective. CORE-VNS began in 2018, so until the first quarter of 2020 participants were able to attend follow-up visits in person according to standard programming and titration schedules. During lockdowns imposed during the pandemic, some participants missed titration visits, or these visits were delayed. While participants with newer programming features like scheduled programming may have been less impacted, concern remains regarding the impact of these titration delays on therapeutic efficacy. A subgroup analysis by enrolment year may clarify the extent of this impact.

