### Study status

To date, 823 participants have been enrolled in the registry at 61 centres. Enrolment closed by the start of June 2021. Follow-up of participants is expected to continue as planned after termination of enrolment.

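### The before-after change in ED and healthcare use is framed as the impact of VNS, although before and after largely coincide with before and after the start of the pandemic

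*Protocol article*

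**What the plan says.** The aim is in the section on healthcare resource utilisation by people receiving VNS: "We will assess, on a regional basis, how VNS impacts ED utilisation and overall healthcare utilisation". The earlier section on healthcare resource utilisation describes the data. Seizure-related ED visits, hospitalisations and length of stay "that have occurred since the previous visit are collected at each visit", and for the starting point, "At the baseline visit, these outcomes are collected through the previous 12 months".

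The Statistical analysis section plans absolute values and changes from baseline with 95% confidence intervals for each clinical endpoint at each visit, and states: "Principal analysis of the full cohort data will occur at 3 years of follow-up". Design limitations names the lack of a parallel group without VNS as the primary limitation and says that benefit can be judged only against the participant's own baseline.

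On calendar time, Design limitations says: "CORE-VNS began in 2018, so until the first quarter of 2020 participants were able to attend follow-up visits in person". Study status adds: "Enrolment closed by the start of June 2021". Design limitations accepts that COVID-19 affected recruitment and follow-up. It carries the concern forward only to delayed titration and its effect on efficacy, and says that a subgroup analysis by enrolment year may help to show the extent.

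**The concern.** When everyone is treated and the contrast is before versus after, whatever changed over calendar time is part of the estimate. The propensity matching mentioned under Ethics and dissemination balances treatment groups against each other. It does nothing for a contrast within the same people over time.

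Here the calendar shift is not a slow drift. The baseline count looks back 12 months from a visit at or before implant, and the follow-up counts run forward from it, so the start of the pandemic falls mainly between the two. If seizure-related attendance changed with the era, the change would be reported as what VNS did. If it changed differently by country, it would appear as a regional difference in VNS benefit. The Methods and analysis section names regulators and payers or commissioners among the intended users.

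The article sees COVID-19 as a threat to titration and efficacy, but does not carry it to the outcome that counts hospital contacts.

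**Working it through.** The article states no calendar share or utilisation effect, so there is no figure to reproduce. The check asks how much of each counting window lies after onset.

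**Inputs**
- Start of registry: 2018, month not given. Base case mid-2018 (2018.5); January and end of 2018 also tested (assumption).
- End of enrolment: about 1 June 2021 (2021.417), from Study status.
- Onset: the article says "until the first quarter of 2020 participants were able to attend follow-up visits in person". Base case mid-March 2020 (2020.2); 2020.0 and 2020.25 also tested.
- Windows: 12 months before implant, then years 1, 2 and 3, from "data collection at baseline as well as 3, 6, 12, 24 and 36 months after implant".
- Accrual shape: not given. Base case even; front-loaded, back-loaded and halved after onset also tested. Complete follow-up assumed.

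**Formula.** For implant date t and window [a, b], the share after onset is max(0, b − max(a, 2020.2)) / (b − a), averaged over t. The accrual period is 2021.417 − 2018.5 = 2.917 years.

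**Base case**
- Baseline [t−1, t]: the share rises from 0 to 1 for implants from 2020.2 to 2021.2, then stays at 1. (0.5 + 0.217)/2.917 = 0.246.
- Year 1 [t, t+1]: (0.5 + 1.217)/2.917 = 0.589.
- Year 2 [t+1, t+2]: implants from 2018.5 to 2019.2 have shares from 0.3 to 1, mean 0.65. (0.65 × 0.7 + 2.217)/2.917 = 0.916.
- Year 3 [t+2, t+3]: the earliest window opens at 2020.5, so the share is 1.00.

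The look-back really ends at the baseline visit, up to 45 days (0.123 year) before implant. If every visit were that early, the baseline share would be (0.5 + 0.094)/2.917 = 0.20, so 25% is if anything high.

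**Sensitivity: per cent after onset**

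| Scenario | Baseline | Year 1 | Year 2 | Year 3 |
|---|---|---|---|---|
| Even accrual, start Jan 2018, onset 2020.2 | 21 | 50 | 80 | 99 |
| Even accrual, start mid-2018, onset 2020.2 | 25 | 59 | 92 | 100 |
| Even accrual, start end 2018, onset 2020.2 | 30 | 71 | 99 | 100 |
| All shapes and starts, onset 2020.2 or 2020.25 | 5–49 | 24.5–90 | 62–100 | 98–100 |

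Only back-loaded accrual, with onset at 1 January 2020 and a start from mid-2018 on, puts most of the baseline after onset (52% to 60%). Years 2 and 3 are then 99.5% to 100% after onset, so the imbalance remains.

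**What an era effect would do.** Suppose VNS has no effect and use falls by a fraction d after onset and stays down. The expected rate ratio against baseline is (1 − d × follow-up share)/(1 − d × baseline share). The values of d are assumptions.

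| d | Year 1 | Year 2 | Year 3 |
|---|---|---|---|
| 0.1 | 0.96 | 0.93 | 0.92 |
| 0.2 | 0.93 | 0.86 | 0.84 |
| 0.3 | 0.89 | 0.78 | 0.76 |

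For d = 0.2 at year 3: 0.8/(1 − 0.2 × 0.246) = 0.8/0.951 = 0.84. If the fall lasts only 12 to 18 months, the same calculation with a closed era gives about 0.92 to 0.99 in year 1 and 1.00 to 1.05 in year 3. Even the direction depends on the assumption.

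**What the enrolment-year split can do (base case, per cent after onset)**

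| Implant year | Baseline | Year 1 | Year 3 |
|---|---|---|---|
| 2018 | 0 | 0 | 100 |
| 2019 | 0 | 32 | 100 |
| 2020 | 32 | 98 | 100 |
| 2021 | 95 | 100 | 100 |

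Baseline and year 1 both lie wholly before onset for implants up to 2019.2: 0.7/2.917 = 24%, roughly 200 of 823. Baseline and year 3 both lie wholly after onset only for implants from 2021.2: 0.217/2.917 = 7.4%, about 60 of 823 across 15 countries.

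**The case against.** The aim is one sentence among exploratory topics in an unpowered, largely descriptive registry, and it fixes no model. The change-from-baseline summary is written for clinical endpoints, and whether it governs ED counts is arguable, although the visit schedule lists healthcare utilisation among the assessments. Calendar terms and count models normally belong in the analysis plan, which exists but is not shown. This stands: the lack of such a model in the article is not a fault. What remains is what the article does say, namely a causal verb on an uncontrolled contrast and a COVID-19 check pointed at other outcomes.

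The article also discloses a good deal. It calls the missing comparator its primary limitation and says that COVID-19 affected both recruitment and follow-up. That is fair, but neither caveat is carried to the utilisation aim.

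A reader might infer that the enrolment-year subgroup is useless because follow-up always comes later than baseline. The table above does not support that. Implants in 2018 have baseline and year 1 wholly before onset, and implants in 2021 lie almost wholly after it. The split is a useful partial check, but it is optional and not tied to utilisation.

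A reader might also infer that a model with half-yearly calendar terms would separate era from time since implant. The article describes totals per interval and mentions no event dates, so such terms cannot be assigned directly. At year 3 nearly everyone is after onset.

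**Conclusion.** The point holds in structure. Under every accrual shape, start month and onset date tested, far more of years 2 and 3 than of the baseline lies after onset. In the base case the shares are 25% at baseline, 59% in year 1, 92% in year 2 and 100% in year 3. An unadjusted change at the principal three-year analysis therefore cannot be attributed to VNS alone.

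Three stronger readings are not supported. Year 2 cannot be called almost wholly post-onset, because its share depends on unstated accrual (62% to 100%); only year 3 is firm. The article does not show that seizure-related ED or hospital use changed with the era, so neither the size nor the direction of any bias is established, and the rate ratios of 0.76 to 1.05 are illustrations. Nor does it show that results have been or will be misread, since none are reported.

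This is a cheap improvement worth making to an exploratory outcome, not a defect in the registry's main safety and seizure summaries.

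**What to change.** 1. In the section on healthcare resource utilisation by people receiving VNS, describe the result as a change from baseline. State that the unadjusted change, above all in years 2 and 3, is not attributable to VNS alone.
2. Extend the COVID-19 check in Design limitations to ED visits, hospitalisations and length of stay, and make it a committed analysis. Report rates by enrolment year or era. Also report the change restricted to participants whose baseline and follow-up intervals lie on the same side of the first quarter of 2020: for example, baseline against year 1 in implants from 2018 to early 2019, and implants in 2021 with a post-onset baseline. Note for the latter that their baseline falls soon after onset, so a recovery in attendance could bias them the other way.
3. As a sensitivity analysis only, fit a within-participant count model (Poisson or negative binomial) with a log person-time offset, time since implant, and the fraction of each interval after onset, by broad region. That fraction can be computed from visit dates already held; half-year terms would need event dates.

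The cost is revised wording, some extra tables and one more model, with no new data collection. The same-era subsets are small (about 24% of the cohort for year 1 before onset and 7% for year 3 after it, in the base case), so intervals will be wide and regional results thin. Era and time since implant can hardly be separated at year 3, and the report should say so.

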### VNS and sleep quality

VNS has been reported to exacerbate and/or induce sleep apnoea in multiple independent case series.^20–22^ Apnoeic events are known to decrease quality of sleep and overall health outcomes. At the same time, uncontrolled epilepsy can impact sleep quality and is associated with increased incidence of obstructive sleep apnoea.^33^ Better understanding of the risk–benefit profile of VNS with respect to quality of sleep and health outcomes seems warranted.

VNS parameters have long been understood to play a role in this adverse effect, and VNS-induced apnoea can be managed by reducing the intensity of stimulation.^34^ Day/night programming was developed in part to help ameliorate apnoeic events through changes in programming parameters during sleep, but the implementation of this technology for reducing incidence of VNS-induced apnoea has not been examined. Therefore, whether day/night programming can improve sleep quality will be investigated. In adult patients, this analysis will be limited to participants with sufficient cognitive ability to provide a complete PSQI as the tool is not validated for use by caregivers.

### The global safety profile of VNS

VNS has been established as a well-tolerated and safe therapy. This finding has been replicated in multicentre randomised controlled trials, registries, single-centre experiences and case series. Most of the global research experience with VNS, however, has occurred in only a few countries. CORE-VNS presents an opportunity to better understand the safety profile of VNS in multiple regions where it has not been previously studied, especially those regions with more recent access to the therapy. Also, certain device components (such as the newest leads) or features (such as responsive VNS) have not been assessed in a comparative fashion versus previous models of these components in a real-world setting.

Patients involved in the study can elect to undergo a device explantation, for any reason. The rationale for explantation is recorded in the case report form associated with that study event. The explantation surgery case report form includes rationale for the explant, such as: death, adverse event(s), lack of efficacy, VNS Therapy no longer desired, MRI, battery depleted, battery nearing depletion, unknown, other.

### Design limitations

Although VNS Therapy has been approved for the treatment of DRE for nearly 30 years, systematic evaluation of its use in the real-world setting has been lacking. The clinical benefits of the latest advances in model features have not been well studied. Given the prospective design, international recruitment and scale, CORE-VNS is ideally suited to generate the much needed long-term evidence to inform the optimal use of modern VNS.

Nonetheless, the study has several limitations. The primary limitation in the protocol design is that the registry only explores the effects of VNS in those who receive it. There is no direct comparison with a parallel group who do not receive VNS. Therefore, the incremental benefit of adding the therapy to a treatment paradigm can only be assessed by comparing with the participant’s own baseline.

The registry did not enrol all patients with VNS. While all sequential patients were considered for enrolment, the inclusion criteria for the study required that subjects and caregivers be willing and able to comply with the frequency of study visits, and assent/consent to participate. Because the inclusion criteria were assessed before the creation of any study documentation linked to a potential participant, no study documentation exists to assess the risk of bias from non-included patients, which could potentially impact the generalisability of the results. Finally, this registry is observational and was not specifically designed to address any of the exploratory analyses described here with adequate statistical power. It is expected that the large size of this registry will help to reduce the risk of undersampling.

There are practice-specific differences in implementation of VNS. The manufacturer’s recommendations on titration and programming may not be closely followed at all centres, including some centres and practices included in the CORE-VNS registry. There are many legitimate, person-centred reasons for this interpractice variability (eg, tolerability, lifestyle) and there are also fundamental differences in hospital-led and company-led training between regions (including regions within the same country). These differences in therapy implementation may confound regional assessment of clinical and safety outcomes. In all regional analyses, careful attention will be paid to marked variance in VNS settings (as compared with global averages based on this study and historical VNS registry data).

The design of CORE-VNS allows for a prospective assessment of programmed settings through the titration window. In many people, these settings are collected in electronic records along with other clinical and safety outcomes data. Such records are not collected at titration visits, which do not assess clinical and safety outcomes. To mitigate this, an electronic capture of the programming history from each programming tablet will be used in the registry. These data will be used to develop a clear picture of the titration period from each site and aim to eliminate the risk of missing data fields in titration logs.

Lastly, COVID-19 has impacted this registry both from a recruiting and follow-up perspective. CORE-VNS began in 2018, so until the first quarter of 2020 participants were able to attend follow-up visits in person according to standard programming and titration schedules. During lockdowns imposed during the pandemic, some participants missed titration visits, or these visits were delayed. While participants with newer programming features like scheduled programming may have been less impacted, concern remains regarding the impact of these titration delays on therapeutic efficacy. A subgroup analysis by enrolment year may clarify the extent of this impact.

### Study status

To date, 823 participants have been enrolled in the registry at 61 centres. Enrolment closed by the start of June 2021. Follow-up of participants is expected to continue as planned after termination of enrolment.
